### Expert evaluation of CHW outputs and LLM outputs

12 independent GPs, each with a minimum of 2 years of clinical experience in Rwanda and valid Rwanda Medical and Dental Council licences, will be recruited for this study. They will be organised into four panels of three to evaluate each patient–CHW consultation transcript using a study-specific evaluation rubric (see online supplemental material 1). This evaluation will provide a ground truth against which the LLM and CHW outputs will be measured. Evaluators will receive training to standardise the evaluation approach. This training will include an overview of the study protocol and detailed instructions on using the evaluation rubric. During the training, 10 simulated cases will be reviewed to establish a common frame of reference across the panel and to familiarise evaluators with the rubric.

Everyone in the triplet group of evaluators will independently review the case transcript, make a diagnosis and develop a management plan. The evaluator’s tasks for each objective are as follows:

Based only on the day 0 consultation transcript, a reference standard should be determined to decide on the appropriateness of the CHW and LLM referral decisions.Review the day 0 consultation transcript and the 5-day or 14-day follow-up information to establish a reference standard for evaluating the correctness of the CHW and LLM referral decisions.Assess the diagnostic accuracy of the LLM through:

 Establishing one ‘most likely’ diagnosis based on all the information provided. Independently scoring the appropriateness of the differential diagnosis list according to a prespecified rubric. Assessing whether the diagnosis provided in the counter-referral (or, if unavailable, the panel’s ‘most likely’ diagnosis) is the top-ranked or is included within the top five differential diagnoses suggested by the LLM.

4. Assess the appropriateness of the LLM-generated management plan according to the evaluation rubric.

After the initial assessments, the average response for the Likert scale question will be calculated. The panel will also review and discuss the open-ended responses, such as the ‘most likely’ diagnosis, and collaboratively reach a consensus on the diagnosis.

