### Secondary outcomes

Compare the appropriateness of CHW referral decisions vs the LLM referral decisions, using the patient’s 5-day or 14-day outcome and counter referral results as the reference standard.

A secondary assessment of referral decision appropriateness will be performed incorporating patient outcomes at day 5 or day 14 follow-up. For each patient, the expert panel will review both the day 0 consultation transcript and subsequent follow-up outcome data to determine whether the initial referral decision was appropriate in retrospect. The CHW and LLM decisions will again be compared with this revised reference standard.

2. Assess the diagnostic accuracy of the LLM as:

Appropriateness of the differential diagnosis list—The expert panel will rate the quality of the LLM-generated differential diagnosis list for each case using a predefined 5-point Likert scale rubric, assessing alignment with medical consensus, knowledge recall, omission of important differentials and inclusion of irrelevant differentials (see online supplemental material 1).Diagnostic accuracy (top-1 and top-5): For consultations where a definitive diagnosis can be established (either via health centre counter-referral or expert panel consensus), the proportion of cases in which the correct diagnosis appears as the LLM’s top-1 diagnosis or within its top-5 ranked differentials will be reported.

3. Assess the appropriateness of the LLM-generated management plan.

The quality of the LLM’s proposed management plans will be independently evaluated by the expert panel using a 5-point Likert scale predefined rubric, rating appropriateness across five domains including alignment with medical consensus, omission of important information, potential for demographic or contextual bias, likelihood of potential harm, contextual appropriateness relative to available resources for CHWs in Rwanda (see online supplemental material 1).

4. Explore the experience and perspectives of patients and CHWs on being recorded during consultation.

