### Secondary outcome analysis

Referral decision appropriateness will be reassessed following integration of day 5 and day 14 follow-up outcome data. The expert panel’s revised appropriateness assessment incorporating these outcomes will serve as an updated reference standard. Diagnostic accuracy metrics and paired comparisons will be repeated against this outcome-informed standard.

For cases with a definitive diagnosis established through expert panel consensus or counter-referral documentation, the proportion of correct diagnoses appearing as the LLM’s top-1 and within its top-5 differential diagnosis list will be reported, with 95% CIs.

Outcomes of interest (appropriateness of differential diagnosis and appropriateness of management plan) will each be measured on a 5-point Likert scale. Distributions of these Likert scale responses will be displayed using frequency tables, numerically summarised across interactions using the median, along with upper and lower quartile values, and visualised using histograms, demonstrating the proportion of interactions rated to be at each level of the scale. For each secondary outcome separately, a multilevel ordinal regression model will be fit, adjusting for important consultation features, with a random effect on the intercept term to account for the natural clustering of the data, as discussed above. Secondary outcome involving measuring the top-1 and top-5 diagnostic accuracy for a subset of participants where a definitive diagnosis was made. The mean (median) rank of the ground truth diagnosis in the differential list will also be summarised.

The patient and CHW user experience questions will be analysed with descriptive analysis to assess the acceptability and impact of recordings. Qualitative responses from CHWs will be thematically analysed to generate themes.

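### Averaging three 5-point ratings gives 13 possible values, which does not fit the per-level displays and 5-point ordinal outcome planned, and the model has no rater term

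*Protocol article*

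**What the plan says.** Under Expert evaluation of CHW outputs and LLM outputs, the protocol article recruits 12 GPs: "They will be organised into four panels of three to evaluate each patient–CHW consultation transcript". Each member of a triplet first scores alone. Then "the average response for the Likert scale question will be calculated". A consensus step is described separately, and not for the Likert items: "The panel will also review and discuss the open-ended responses".

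Under Secondary outcomes, the LLM's differential list is rated "using a predefined 5-point Likert scale rubric", and its management plan "using a 5-point Likert scale predefined rubric, rating appropriateness across five domains". The rubric items include omissions (both outcomes) and likelihood of harm (management plan).

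Under Secondary outcome analysis, the two outcomes "will each be measured on a 5-point Likert scale". They are to be shown in frequency tables, summarised by median and quartiles, and plotted in histograms "demonstrating the proportion of interactions rated to be at each level of the scale". For each outcome "a multilevel ordinal regression model will be fit", with one random intercept for the natural clustering. Primary outcome analysis defines that clustering by CHW. No rater or panel term is named.

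**The concern.** The two sections describe different variables. One produces an average per consultation. The other treats each consultation as sitting on one of five ordered levels. A mean of three integer scores usually does not fall on such a level, so the per-level displays cannot be produced from it as written, and the analyst would have to choose a conversion after seeing the data.

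Two further losses follow from the averaging. First, the mean cannot distinguish agreement from disagreement. That matters most for harm and omission, where one GP's extreme rating is the information a safety reading needs, and the Introduction says that the findings will inform safety. Second, all ratings come from 12 GPs, who may differ in severity. One averaged value per consultation, with a random effect for CHW only, leaves no place to estimate that difference.

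**Working it through.** The plan states no figure on this point, so there is none to reproduce. Inputs from the article: 3 raters per consultation, scores 1 to 5, 12 GPs, 800 consultations, about 10 per CHW. Everything marked as assumed below is not in the document.

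**Possible values.** The sum of three scores runs from 3 to 15, which is 15 − 3 + 1 = 13 values. The mean is sum/3: 1, 4/3, 5/3, 2, …, 5. Only sums 3, 6, 9, 12 and 15 give a whole number, so 5 values are scale levels and 8 are not. This part needs no assumption.

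**How often.** This depends on the spread of ratings and on agreement, both assumed. For independent raters the share comes from summing the probabilities of all 5³ = 125 triples whose total is not divisible by 3. For correlated raters it was simulated (400,000 draws; latent normal with a shared consultation component, cut at the assumed spread).

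| Assumed spread over levels 1–5 (%) | Correlation 0 | 0.3 | 0.5 | 0.7 | 0.9 |
|---|---|---|---|---|---|
| 20/20/20/20/20 | 67% | 66% | 64% | 61% | 53% |
| 5/10/20/40/25 | 67% | 66% | 65% | 61% | 48% |
| 2/5/13/40/40 | 69% | 65% | 62% | 56% | 41% |

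Across the table, 41% to 69% of means are off the scale: 0.41 × 800 ≈ 330 to 0.69 × 800 ≈ 550 consultations. More concentrated ratings lower the share. With 1/2/5/22/70 it is 56% at correlation 0 and about 27% at 0.9.

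**What the mean hides.** A mean of 3 arises from (3,3,3), (2,3,4), (1,4,4), (2,2,5) and (1,3,5). Under the first and third spreads, at correlations 0.3 to 0.9, between 2% and 26% of consultations have a whole-number mean although the raters disagree.

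**Can the regression run?** A cumulative-logit model without the random intercept was fitted to 800 simulated unrounded means. It converged with 13 ordered levels.

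**Rater severity and standard errors.** Illustration for the overall mean rating. Assumptions: one panel per consultation, panels equally loaded, CHW intraclass correlation 0.05, and rater severity a share s of the single-rating variance V.

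- Variance from CHW clustering, at most: V × [1 + (10 − 1) × 0.05]/800 = 1.45V/800.
- Added variance from 12 raters: sV/12.
- Ratio of standard errors, at least: √[1 + (s/12)/(1.45/800)] ≈ √(1 + 46s).
- s = 0.02, 0.05, 0.10 gives about 1.4, 1.8, 2.4.

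This applies when the rating level is meant to hold for GPs beyond these 12.

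**The case against.** The strongest reply is that this needs only a clarification. The article does not define the average. If it meant the median, three integer scores would always give a scale level and the mismatch would vanish. A conversion rule, or more detail on random effects, may sit in the statistical analysis plan or in the supplement with the rubric, neither of which is shown. The outcomes are secondary, rate the LLM alone, and carry no stated hypothesis test. Rater training on 10 simulated cases aims at a common frame of reference.

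Much of this is fair, and it limits the size of the point. The mean remains the natural reading, because the same analysis section names mean and median as different things when it summarises diagnosis rank. The point rests on two rules that the article states, not on missing detail. A conversion rule elsewhere would reconcile the levels but would not bring back the disagreement lost by averaging.

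Four stronger readings are tempting and are not supported:

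- *The ordinal regression cannot be fitted.* It can: it needs ordered categories, not five integers. Medians and quartiles also accept thirds.
- *Rounding the means would pull scores to the centre.* No rounding rule is in the article, and rounding has no such direction: 3.33 and 4.33 go inward to 3 and 4, but 3.67 and 4.67 go outward to 4 and 5. The shrinkage comes from averaging.
- *All standard errors are too small.* For covariate contrasts, such as paper against app, the effect depends on how consultations are allocated to panels, which the article does not give. With balanced allocation it need not arise.
- *Individual ratings are thrown away.* Nothing says so. They are made independently; the described analysis simply does not use them.

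**Conclusion.** The point stands in limited form. With the average read as the mean, the evaluation rule yields 13 values, 8 of them off the scale, and this does not match an analysis defined on five levels. The per-level displays cannot be produced from such averages as written. The regression can run, but as a 13-level model, possibly with sparse levels, and not as a model of the 5-point outcome. The count of 13 is arithmetic. The share of consultations affected, roughly 41% to 69%, rests on assumed spreads and correlations and would be lower if ratings cluster heavily at one end.

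The loss of disagreement on harm and omission follows directly from averaging. The understated standard error is conditional: it concerns overall rating levels generalised beyond the 12 GPs, and its size depends on a rater variance that the document does not give. The primary referral outcome and the top-1 and top-5 accuracy are not touched. The point should be settled before analysis, but it does not threaten the main comparison.

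**What to change.** For the two Likert secondary outcomes, replace the averaging rule as follows:

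1. Analyse the three individual ratings per consultation in a cumulative-logit mixed model with random effects for consultation, CHW and rater, keeping the planned consultation covariates.
2. For frequency tables and histograms, use the median of the three ratings, which is always a scale level.
3. For the harm and omission domains, also report the most adverse of the three ratings.

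The ratings are already made independently, so no new data are needed and the change is one of analysis wording. The price is a somewhat more complex model, and a rater variance estimated from only 12 GPs, which will be imprecise and should be reported with its uncertainty.

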### Primary outcome

The primary outcome of this study is the appropriateness of referral decisions made by CHWs and by the LLM, measured against the consensus decision of an independent expert clinical panel, according to the day 0 consultation transcript only.

For each patient consultation, both the CHW’s actual referral decision on whether to refer the patient to a health facility or manage them in the community and the LLM-generated referral decision will be compared with the reference standard established by a blinded evaluation panel of GPs, based solely on the information available in the day 0 consultation transcript.

### Secondary outcomes

Compare the appropriateness of CHW referral decisions vs the LLM referral decisions, using the patient’s 5-day or 14-day outcome and counter referral results as the reference standard.

A secondary assessment of referral decision appropriateness will be performed incorporating patient outcomes at day 5 or day 14 follow-up. For each patient, the expert panel will review both the day 0 consultation transcript and subsequent follow-up outcome data to determine whether the initial referral decision was appropriate in retrospect. The CHW and LLM decisions will again be compared with this revised reference standard.

2. Assess the diagnostic accuracy of the LLM as:

Appropriateness of the differential diagnosis list—The expert panel will rate the quality of the LLM-generated differential diagnosis list for each case using a predefined 5-point Likert scale rubric, assessing alignment with medical consensus, knowledge recall, omission of important differentials and inclusion of irrelevant differentials (see online supplemental material 1).Diagnostic accuracy (top-1 and top-5): For consultations where a definitive diagnosis can be established (either via health centre counter-referral or expert panel consensus), the proportion of cases in which the correct diagnosis appears as the LLM’s top-1 diagnosis or within its top-5 ranked differentials will be reported.

3. Assess the appropriateness of the LLM-generated management plan.

The quality of the LLM’s proposed management plans will be independently evaluated by the expert panel using a 5-point Likert scale predefined rubric, rating appropriateness across five domains including alignment with medical consensus, omission of important information, potential for demographic or contextual bias, likelihood of potential harm, contextual appropriateness relative to available resources for CHWs in Rwanda (see online supplemental material 1).

4. Explore the experience and perspectives of patients and CHWs on being recorded during consultation.

User experience outcomes will assess the acceptability and perceived impact of consultation recording for both patients and CHWs. Immediately after each recorded consultation, patients will complete a brief questionnaire rating their comfort being recorded, perceived effects on communication and consultation thoroughness, and the perceived naturalness of the consultation process (see online supplemental material 1). At the end of the study, CHWs will complete a questionnaire assessing their perceptions of patient comfort, impact of recording on care delivery, ease of using the StudyApp and the need for additional training or technical support. A subset of CHWs will also participate in focus group discussions to explore their experiences in greater depth (see online supplemental material 1).

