Patient participants will be excluded from the study if they are receiving CHW visits for reasons other than new health-related complaints, such as weight checks, vaccinations or routine antenatal care. Patients requiring immediate or emergency medical care, including trauma cases and medical emergencies, will also be excluded. Additionally, non-verbally communicative participants, those in consultation environments that do not allow for audio recording, and patients who do not speak Kinyarwanda or English will not be eligible. Finally, patients who are unable or unwilling to be contacted for follow-up outcomes or to attend a health centre if referred will be excluded from participation.

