### Consultation and related events

On consent, the CHW will initiate audio recording of the entire clinical consultation using the StudyApp. CHWs will be instructed to conduct consultations according to their usual practice, guided either by the national CHW decision-making algorithm (on paper or via CHWApp). The consultation recording—and all subsequent LLM outputs—will not be used to influence the care of the patient. The CHW will be asked to provide their usual standard of care, and there are no restrictions placed on that care as a result of this study. Following the consultation, CHWs will administer a brief structured patient experience questionnaire to assess perceptions of being recorded (see online supplemental material 1).

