### Follow-up and related events

As part of standard CHW practice, patients will be followed up on day 5 to assess symptom progression and treatment outcomes. In addition, the study protocol includes a day 14 follow-up for research purposes. CHWs will complete a structured follow-up form (see online supplemental material 1) on the StudyApp, capturing information on symptom resolution (resolved, unchanged, worsened, deceased), any further health service use and counter-referral details for referred patients.

Patients reporting full symptom resolution at the day 5 follow-up will not undergo the day 14 follow-up. CHWs will also photograph and upload any counter-referral forms (providing feedback to the CHW for continued care in the community) received from health centres for referred patients (see online supplemental material 1).

After the data collection period, RAs will conduct short user experience surveys and four focus group discussions of 8–12 CHWs to get insight into their experience of being recorded and any challenges faced (see online supplemental material 1).

Patient participant flow is summarised in figure 1.

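### The outcome-informed referral reference arises only under the CHW's enacted decision, so the repeated paired LLM versus CHW comparison carries a bias of unknown direction

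*Protocol article*

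**What the plan says.** The Secondary outcomes section of the protocol article names the patient's "5-day or 14-day outcome and counter referral results as the reference standard" for comparing CHW with LLM referral decisions. The panel reads the day 0 transcript together with the follow-up data "to determine whether the initial referral decision was appropriate in retrospect", and both decision makers are scored against the result. Under Secondary outcome analysis, "Diagnostic accuracy metrics and paired comparisons will be repeated against this outcome-informed standard".

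Three other statements fix how those data arise:

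- Consultation and related events: the recording and the LLM outputs "will not be used to influence the care of the patient". Only the CHW's decision is acted on.
- Eligibility criteria and recruitment: patients "unable or unwilling to be contacted for follow-up outcomes or to attend a health centre if referred will be excluded from participation". Referrals are therefore expected to be taken up.
- Follow-up and related events: the follow-up form records symptom status, plus "any further health service use and counter-referral details for referred patients". In addition, "CHWs will also photograph and upload any counter-referral forms".

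The primary outcome is different. Its reference uses the day 0 transcript only, and the panel is described there as blinded.

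**The concern.** One of the two decision makers helps to generate the standard by which both are judged. The day 5 or day 14 status is what happened after the CHW's choice was carried out, and a counter-referral result can exist only if the patient was referred. A paired accuracy difference is driven entirely by cases where CHW and LLM disagree. In every such case the course under the LLM's choice is unobserved.

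This can push the result either way:

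- A patient who needed referral, was referred, was treated and recovered may be judged in retrospect not to have needed it. That penalises the CHW and rewards an LLM that would have kept the patient at home.
- A patient who needed referral, was not referred and recovered anyway may be re-labelled in the CHW's favour.
- A panel that can tell what was done may lean towards endorsing it, which also favours the CHW.

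What is at stake is interpretation. A result described as outcome-informed may be read as stronger evidence than the primary comparison, although it mixes decision quality with the effect of care given and with hindsight.

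**Working it through.** The plan gives no figure for this point, so there is none to reproduce. The dependence follows from the sections cited above. The arithmetic only shows what size it could have.

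**Inputs.** CHW accuracy c = 0.733 is the Sample size section's assumption. The following are my assumptions, because the article does not state them: the share of patients who need referral, p = 0.2 or 0.4; LLM accuracy l; LLM and CHW errors independent given true need; accuracy equal in patients who do and do not need referral; and the re-labelling rates below. Each route is taken alone.

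**Route A: needed, referred, recovers, re-labelled as not needing referral, at rate a.** The affected share is p·c·a. The CHW loses all of it; the LLM changes by p·c·a·(1 − 2l). Shift in LLM minus CHW = 2·p·c·a·(1 − l).

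**Route B: needed, not referred, recovers anyway, re-labelled, at rate b.** Shift = −2·p·(1 − c)·b·l.

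**Route C: panel adopts the enacted decision, at rate g.** Difference = (1 − g)(l − c) − g·[1 − P(agree)], with P(agree) = l·c + (1 − l)(1 − c).

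**No true difference (l = c = 0.733).**

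| Route | Rate | p | Calculation | Apparent difference (points) |
|---|---|---|---|---|
| A | 10% | 0.2 | 2 × 0.2 × 0.733 × 0.1 × 0.267 | +0.8 |
| A | 30% | 0.2 | 2 × 0.2 × 0.733 × 0.3 × 0.267 | +2.3 |
| A | 10% | 0.4 | 2 × 0.4 × 0.733 × 0.1 × 0.267 | +1.6 |
| A | 30% | 0.4 | 2 × 0.4 × 0.733 × 0.3 × 0.267 | +4.7 |
| B | 10% to 30% | 0.2 | same products, negative | −0.8 to −2.3 |
| B | 10% to 30% | 0.4 | same products, negative | −1.6 to −4.7 |
| C | 10% | any | −0.1 × (1 − 0.6086) | −3.9 |
| C | 20% | any | −0.2 × (1 − 0.6086) | −7.8 |

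Here P(agree) = 0.733² + 0.267² = 0.6086. Simulating 1,000,000 consultations gives the same values to within about 0.1 point. The span is about −8 to +5 points. Routes acting together could offset each other (A and B cancel exactly at equal rates and equal accuracies) or add up.

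**True LLM advantage of 15 points (l = 0.883).** P(agree) = 0.883 × 0.733 + 0.117 × 0.267 = 0.6785.

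- Route C at 20%: 0.8 × 0.15 − 0.2 × 0.3215 = 0.056, or 5.6 points.
- Route A at 30% with p = 0.4: 0.15 + 2 × 0.4 × 0.733 × 0.3 × 0.117 = 0.171, or 17.1 points.

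For scale, the Sample size section gives 11.8 points as the smallest difference the study can detect.

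**Does anything in the article remove the dependence?** The Primary outcome section ties blinding to the day 0 reference. Removal of the CHW's management and referral decision is described under LLM output generation for the LLM's input only. The primary comparison runs on the full data, and the one consultation factor named for adjustment is paper versus app. That the secondary comparison is likewise pooled is an inference from the word for repeating it. The stated limitation on patient outcomes concerns clinical impact, not this reference.

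**The case against.** Several points on the other side have force.

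- **The label is not mechanical.** The panel weighs the transcript as well as follow-up. A counter-referral can carry a facility diagnosis, so a treated patient with a documented serious condition need not look like an unnecessary referral. This stands: counter-referral is evidence of need as well as a sign of what the CHW did. It limits the size of the distortion but does not supply the missing outcome under the LLM's choice.
- **The rubric is in a supplement that is not shown and may contain masking.** True, but masking could not remove the dependence altogether, because the counter-referral result is itself part of the named reference and symptom status reflects the care received.
- **Only a secondary outcome is involved, and the article states no superiority claim from it.** Both are correct, and they limit the weight of the point.

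A reader might go further and infer that the comparison understates the LLM. With the benchmark accuracies of 73.3% and 91.2% and independent errors, the LLM alone is right in 0.912 × 0.267 = 24.35% of cases and the CHW alone in 0.733 × 0.088 = 6.45%, a difference of 17.9 points. If the panel sided with the enacted decision in 10% or 20% of the LLM-right cases, that would fall by 2 × 0.10 × 24.35 = 4.9 points or 2 × 0.20 × 24.35 = 9.7 points, to 13.0 or 8.2. The arithmetic is sound but it models one direction only. Flipping 10% or 20% of the CHW-right cases would add back 2 × 0.10 × 6.45 = 1.3 or 2 × 0.20 × 6.45 = 2.6 points, and the documents fix none of these rates.

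A reader might also infer that counter-referral forms unblind the panel. The article does not support that as a firm claim: it does not say whether the panel's transcript has the CHW decision removed, and since only forms received are uploaded, a missing form does not prove non-referral.

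**Conclusion.** The point holds as a limit on what one secondary comparison can show. The outcome-informed reference depends on the CHW's enacted decision, nothing in the article corrects for that, and the repeated paired difference cannot be read as a difference in decision quality. The direction is unknown. Under the assumed rates, one route at a time, a true difference of zero could appear as about −8 to +5 points, and a true 15-point LLM advantage as about 5.6 to 17.1. These figures illustrate possible size; they rest on assumed prevalence, independent errors and assumed re-labelling rates.

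A reader might conclude that the study's main result is compromised, or that this comparison must be dropped. Neither follows. The primary reference uses the day 0 transcript alone and is untouched by this mechanism, and the comparison is a named secondary objective that can be kept if it is labelled for what it is. This is a cheap improvement.

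**What to change.** Keep the comparison, and in the analysis plan:

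1. Label it exploratory and draw no LLM-versus-CHW superiority conclusion from it.
2. State that outcomes under an LLM decision that was not enacted are unobserved.
3. Report results separately by CHW decision (referred, not referred) and by LLM-CHW agreement. Among non-referred patients who worsened, died or sought further care, give the share the LLM would have referred.
4. Tabulate the number and direction of panel revisions from the day 0 judgement, by CHW decision. This shows directly how far follow-up moved the reference and which way.

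The split in item 3 should stay descriptive. In particular, non-referred patients who resolved and whom the LLM would have referred should not be counted as LLM errors, since their resolution was observed only under the CHW's decision.

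The cost is wording and a little more tabulation from fields already collected: symptom status, further service use, counter-referral details and the two panel judgements. The downside is a less prominent headline difference for this secondary outcome.
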